## Abstract

**Background:**

Healthcare workers represent one of the most affected categories by the adverse effects of the COVID-19 pandemic on mental health. Excessive stress and anxiety are critical factors that could compromise work performance. Besides, high levels of stress and anxiety may have long-term physical and psychological consequences. Recent studies investigated virtual reality to reduce stress and anxiety among healthcare workers during the COVID-19 pandemic. However, the proposed virtual reality interventions have important limitations related to their location (i.e., research lab and hospitals) and content (i.e., virtual experiences only for relaxation). Within this context, this randomized controlled trial aims to investigate the efficacy and acceptability of a brief home-based virtual reality training for managing stress and anxiety during the COVID-19 crisis in a sample of Italian healthcare workers.

**Methods:**

The study is a randomized controlled trial. It includes two groups of 30 individuals recruited from healthcare workers: (1) the experimental group and (2) the control group. Participants in the experimental group will receive a training consisting of three home sessions performed in a week. In each session, participants will try through an immersive virtual reality standalone system (i.e., Oculus Quest 2) a virtual psychoeducation experience on stress and anxiety (i.e., MIND-VR). Subsequently, they will try the virtual relaxation content (i.e., The Secret Garden). The control group will receive no training and will be reassessed one week and one month after the initial evaluation.

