### Strategies for monitoring and improving intervention protocol adherence

All participants will be invited to contact the research psychologist as needed. Participants in the experimental group will be provided with a log book to record technical problems, safety issues, and the date and time they used VR during the intervention. Besides, the research psychologist will monitor the intervention adherence using remote access to the online questionnaires dataset. Participants who will not have completed the pre- and post-training session scales on the scheduled dates will receive an email and a text message encouraging them to use VR. Furthermore, the psychologist will send an email and a text message to remind participants to complete the post-intervention and follow-up assessment, respectively, at the end and 1 month after the intervention. Participants in the experimental group will also be reminded to participate in the post-training session. The psychologist will contact via a phone call those who will not fill out online questionnaires at the scheduled times and individuals in the experimental group who will not attend the post-training session.

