#### Experimental group

Participants in the experimental group will receive the home-based VR intervention. Following a description of the protocol in detail:*Intake session (session 1):* after signing the informed consent and completing the baseline questionnaire accessible online (i.e., demographic, ad hoc questionnaire about the use of technological solutions and VR, ad hoc questionnaire on the level of exposure to COVID-19, FCOR, ad hoc questionnaire on stress and anxiety management, PSS-10, STAI-Y2, DASS-21, ad hoc questionnaire on knowledge of stress and anxiety), participants will receive from the research psychologist an explanation about the aims and methods of the home-based VR program. Participants will be asked for their involvement and availability during a week to allow in-home training. The psychologist will remind participants to perform the training three per week, with a distance of 2 days between one session and another. Then, individuals will receive information about the safety and hygiene procedures to prevent COVID-19 infection (see Table 3). The psychologist will give participants the Oculus Quest 2, a consumer-grade standalone VR system that consists of an HMD and two controllers. Individuals will wear the headset and receive a short 15-min training on using the VR system. In particular, they will try the tutorial content available on the Oculus Store. Furthermore, individuals will receive a link to complete the online questionnaires (i.e., STAI-Y1, VAS-A) before and after each session. They will be provided with a log book in which to record technical problems, safety issues, and the date and time they used VR during the intervention. Finally, the research psychologist will schedule the date of the post-training session.*Training sessions (sessions 2, 3, and 4):* they will consist of three home sessions of approximately 30 min each, conducted in a week with a distance of 2 days between one session and another. Participants will try for about 15 min one path of the virtual psychoeducational experience MIND-VR in each session (see Fig. 2). Subsequently, they will use for about 10 min the virtual relaxation content The Secret Garden. Individuals will be asked to complete online the VAS-A and the STAI-Y1 at the beginning and the end of each session.*Post-training session (session 5):* the research psychologist will meet participants for the post-intervention interview at the end of the training. On this occasion, participants will return the Oculus Quest 2, which will undergo specific procedures to avoid contamination by COVID-19. Participants will be asked to complete within 1 week after completion of the intervention the online questionnaires (i.e., PSS-10, STAI-Y2, DASS-21, ad hoc questionnaire on knowledge of stress and anxiety, SUS, SDM, NPS, ad hoc questionnaire on difficulties and adverse effects).*Follow-up session (session 6):* the PSS-10, STAI-Y2, DASS-21, and the ad hoc questionnaire on knowledge of stress and anxiety will be conducted after a 1-month follow-up.

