Finally, during the post-training session, participants of the experimental group will be interviewed for about 15 min. The questions will be based on the methodology used in a recent study [51]: Were there any features that you especially liked in using the home-based VR training? Were there any features you did not like or found useless? Have you ever had to stop using VR, and if so, why? Have you learned anything using MIND-VR and The Secret Garden? Were there any features of the VR experiences more valuable than others? Would you like to have more sessions with this type of training? Do you have any questions or would like to add anything?

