### Ethics

During the post-training session, participants of the experimental group will have a debriefing with the research psychologist. Should any participants experience adverse emotional reactions after the session, they will be addressed to appropriate psychological support, and the possibility of withdrawal from the study will be considered. These events will be recorded. Specifically, the time point at which the adverse events occurred, the motivation, and the events’ features (which emotions and with which intensity, which psychophysiological perceptions) will be collected and recorded on the CRF. Any adverse event will be discussed within the project team and assessed individually to identify any variable needing revision within the virtual content. If any substantial protocol modifications are needed because of organizational and/or clinical reasons, the study will be promptly suspended.

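### The protocol gives conflicting times for the post-intervention and follow-up assessments, so the two arms can be measured at different elapsed times, and the VR arm after a psychologist interview that controls do not have

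*Protocol article*

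**What the plan says.** Four places in the protocol article set the timing of the shared primary scales.

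- **Abstract, Methods** (control arm): "The control group will receive no training and will be reassessed one week and one month after the initial evaluation".
- **Experimental group, post-training session:** "Participants will be asked to complete within 1 week after completion of the intervention the online questionnaires". The training itself is "conducted in a week with a distance of 2 days between one session and another". The follow-up scales "will be conducted after a 1-month follow-up", with no starting point named there.
- **Strategies for monitoring and improving intervention protocol adherence:** participants are reminded "to complete the post-intervention and follow-up assessment, respectively, at the end and 1 month after the intervention".
- **Table 2:** one grid for both arms, with baseline at week 0, post-intervention at week 1 and follow-up at week 5.

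The Control group section lists the same three assessments but gives them no anchor or window of its own.

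On contact with the psychologist, the Experimental group section says "the research psychologist will meet participants for the post-intervention interview at the end of the training" and lists the post questionnaires under that same session. The Secondary outcome section says that "during the post-training session, participants of the experimental group will be interviewed for about 15 min", and the Ethics section adds: "During the post-training session, participants of the experimental group will have a debriefing with the research psychologist". Nothing says whether the scales come before or after this meeting.

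**The concern.** The effectiveness test in the Data analysis section is a Group by Time ANOVA in which Time has two levels, pre and post, and elapsed days do not appear. It therefore takes the two arms to be observed over the same interval. If sites apply the abstract's rule to controls and the experimental-arm rule to the VR group, the interval can differ by arm. Randomisation balances the arms at baseline. It does not remove a difference in timing or contact that arises after allocation.

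The outcomes are self-reported, and the PSS-10 is described as a measure of current stress, so both the date of answering and a recent conversation with the psychologist could matter. The interview asks, among other things, whether the participant learned anything from the VR content. The knowledge questionnaire is a listed primary outcome collected in the same window, so the interview could prompt recall in one arm only.

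**Working it through.** **The plan's own schedule.** Table 2's week 5 is one week of training plus a month of four weeks: 7 + 28 = day 35. That agrees with follow-up one month after the intervention. It does not agree with the abstract's one month after the initial evaluation, which is day 28 to 31. The difference is 35 − 31 = 4 to 35 − 28 = 7 days. Likewise, a window that runs to a week past the end of training does not fit a single week-1 time point.

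**Inputs.** Day 0 is baseline. From the abstract, controls are assessed on day 7 and about day 30. From the Experimental group section, there are three sessions with two days between them, and the post window is 0 to 7 days after the last. From the adherence section, follow-up is one month (taken as 30 days) after the intervention.

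**Assumptions.** The document gives no interval from baseline to the first session, so the first session is placed on day s = 0 or 1. The spacing is read either as every second day (g = 2) or as two clear days between sessions (g = 3).

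**Formulas.**
- End of training: E = s + 2g
- VR post window: E to E + 7
- Gap to controls at post: from E − 7 to (E + 7) − 7 = E
- Gap to controls at follow-up: (E + 30) − 30 = E

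| s | g | E | VR post window (day) | Gap at post (days) | VR follow-up (day) | Gap at follow-up (days) |
|---|---|---|---|---|---|---|
| 0 | 2 | 4 | 4 to 11 | −3 to +4 | 34 | +4 |
| 1 | 2 | 5 | 5 to 12 | −2 to +5 | 35 | +5 |
| 0 | 3 | 6 | 6 to 13 | −1 to +6 | 36 | +6 |
| 1 | 3 | 7 | 7 to 14 | 0 to +7 | 37 | +7 |

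Across the four cases the post gap runs from −3 to +7 days and the follow-up gap from +4 to +7 days. Any delay between baseline and the first session moves the VR arm later still. The sample size of 54 does not depend on any of this.

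**Order of interview and scales.** Session 5 contains the interview and the debriefing, and the scales may be completed up to a week after training ends. Answering after the meeting is therefore allowed but not required. Controls have no such meeting.

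**The case against.** The strongest reply is that the body of the protocol points to one schedule. Only one sentence in the abstract gives controls their own anchor. Table 2 does not split the shared scales by arm, the Outcomes section has both groups completing them at the same three named points, and the reminder sentence is worded for participants in general. This stands: a reader might infer a deliberate two-anchor design, and the document does not support that. What it shows is an unreconciled contradiction.

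A reader might also infer that the VR arm is systematically measured up to a week late at post. That does not follow either. The +7 compares the last day of the VR window with the nominal control date. No control window is stated, so controls may also answer late. A VR participant who answers promptly can match controls or be up to 3 days earlier. The one-week allowance may be meant as a tolerance, backed by reminders and phone calls.

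It is also fair that the clearest conflict, at follow-up, lies outside the stated pre/post test. The STAI-Y2 asks how people usually feel, and the VR arm already meets the psychologist at intake, so moving one interview of about 15 minutes would not equalise contact. These points limit the concern. They do not make the stated times compatible.

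**Conclusion.** The point holds as an inconsistency that should be corrected. The stated times cannot all be followed. Applied literally, they put the VR arm's post assessment about −3 to +7 days from the controls' and its follow-up about +4 to +7 days later. This rests on training starting on day 0 or 1 and ending on day 4 to 7. The largest post gap equals the controls' whole 7-day interval, but only in the extreme case.

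Only the post gap enters the stated ANOVA. The document gives no figure for drift in stress or anxiety over days, so neither the size nor the direction of any bias can be computed, and it would be wrong to claim that the Group by Time effect is biased in favour of VR. Completion of the scales after the interview and debriefing is possible but not prescribed. It is an avoidable difference between the arms.

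**What to change.** 1. Reconcile the abstract, the adherence section, the Experimental group section and Table 2 to one schedule counted from a common baseline anchor, for example Table 2's weeks 1 and 5.
2. State the same completion window for both arms, and open the post window only once the one-week training period has ended. A fixed send date on day 7 from randomisation would not be safe. The interval from randomisation to the first session is not stated, so day 7 could fall before the last session. State that interval as well.
3. Have the VR arm complete the online scales before the session-5 interview and debriefing, either beforehand or on arrival.
4. Record each completion date and add a sensitivity analysis that adjusts for days since baseline. It is supportive only: elapsed time arises after randomisation and, if it differs sharply by arm, cannot be separated from the arm effect.

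The cost is changed wording and send dates and a slightly tighter completion window for the VR arm, with no extra visits. Recruitment was ongoing at submission, so the change would apply to participants not yet assessed. Those already assessed can enter the sensitivity analysis where their completion dates are held.

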**Discussion:**

If the proposed brief home-based virtual reality training will result helpful and easy to use, it could become an empirically assessed viable option for protecting healthcare workers’ mental health both during the COVID-19 pandemic and once it will be over. Furthermore, the intervention might be easily adapted for other categories of people who need support in managing stress and anxiety.

**Trial registration:**

ClinicalTrials.gov NCT04611399.

## Introduction

### Background and rationale

After the first reports at the end of December 2019 of unidentified pneumonia cases in Wuhan, China, on March 11, 2020, the World Health Organization (WHO) declared the novel coronavirus (COVID-19) a global pandemic [1]. Healthcare workers represent one of the most affected categories by the adverse effects of the COVID-19 crisis [2–4]. The risk of being infected, exhausting work rhythms, and the need to manage patients experiencing extreme suffering have put hospital staff’s physical and mental health at high risk [2–4].

Several studies and systematic reviews showed that healthcare workers, especially those working in intensive care units (ICU), emergency medicine, infectious disease, and pulmonary medicine, have experienced high levels of stress [4, 5] and anxiety [6, 7] during the outbreak of the COVID-19 pandemic. In Italy, among the first European countries to be hit by the COVID-19 pandemic, healthcare workers showed high levels of stress, anxiety, and depression and an increased risk for post-traumatic stress disorder (PTSD) [8–10]. Similar results have been reported by studies conducted in several countries around the world, including China [11, 12], the USA [13, 14], and India [15, 16].

Excessive stress and anxiety are critical factors that could compromise healthcare workers’ performance [17, 18], particularly during an emergency [19]. Besides, high stress and anxiety levels may have long-term physical and psychological consequences [20, 21]. Therefore, after the COVID-19 outbreak more than ever, urgent actions are needed to offer healthcare workers psychological support [22, 23].

Within this context, new approaches to mental health integrating advanced technologies such as virtual reality (VR) can play a critical role [24–29]. From a technical point of view, VR is a set of technology, including head-mounted display (HMD), computer, and mobile devices, that lets users navigate and interact in real time with a three-dimensional (3D) environment [30, 31]. VR technologies can immerse their users in a virtual environment to different degrees [32]: from a simple presentation on a two-dimensional (2D) display screen system (i.e., desktop VR) to a room-size system (i.e., semi-immersive VR), often referred to by the trade name of C-Automatic Virtual Environment (CAVE), up to highly immersive systems (i.e., immersive VR), that used HMDs. The HMD, a device containing two LCD screens capable of tracking the user’s head motions and position to portray the virtual environments accordingly, is considered the unquestionable leader of immersive VR systems [33]. Such systems can be classified based on the technologies on which they are implemented (Table 1).

**Table 1 Tab1:** Classification of immersive VR systems based on the technologies on which it is implemented

Typology	Definition	Examples
PC-based	Require a connection between an HMD and a computer with advanced computational and graphics capabilities	Oculus Rift S, HTC Vive
Console-based	Need a connection between an HMD and a gaming console	PlayStation VR
Mobile	Consist in the integration of VR on mobile devices thanks to specific HMDs	Low-cost HMDs compatible with mobile phones such as Google Cardboard
Standalone (all-in-one)	They do not need other technologies to work	Oculus Quest 2, HTC Vive Focus, Pico Interactive Neo

VR has been successfully applied in a wide range of mental conditions [34–37], including stress and anxiety [38–41]. VR is effective in inducing relaxation, leading to a positive affective state and reducing stress and anxiety [42–44], with therapeutic benefits similar to or even more significant than those of traditional programs such as cognitive-behavioral therapy (CBT) interventions (e.g., in vivo exposure and guided imagery) [40, 45]. The visual presentation of relaxing virtual scenarios (e.g., naturalistic environments) can facilitate the practice of individuals and the consequent mastery of relaxation techniques [42–44]. VR is also adopted successfully to deliver biofeedback [46, 47] and mindfulness training [48, 49]. Furthermore, VR represents a potentially helpful tool for psychoeducation [50–52] that refers to interventions aimed at informing people about an illness and in a clear and articulated way, educating individuals on their disease and how to deal with it [53, 54]. Psychoeducation is considered a key part of CBT [55] and can also be an intervention of its own [56, 57].

Interestingly, recent studies investigated the use of VR for diminishing stress and anxiety among healthcare workers during the COVID-19 pandemic. VRelax (i.e., 360° videos of calming natural environments watched via an HMD) effectively reduced stress and induced positive emotions in a sample of ICU nurses [58]. Besides, Tranquil Cinematic-VR simulation (i.e., a 3-min 360° immersive video of a nature scene) lowered stress among frontline healthcare workers in COVID-19 treatment units [59].

Although these findings are promising, significant limitations could impact the efficacy and the adoption of the VR interventions proposed in these studies. The first one is related to their location (i.e., research lab and hospitals) [58, 59]. Healthcare workers may be unable or reluctant to participate in face-to-face sessions to use VR, especially at times of crisis, primarily due to workload and variable schedules [60]. Importantly, recent standalone VR systems have made this technology feasible for everyday in-home use [61]. Thanks to this fact, home-based VR programs represent new promising interventions for remote psychological support [61–63], including relaxation training [64, 65]. The second main limitation of VR interventions tested by previous studies is related to their content [58, 59]. Such programs have only used VR for relaxation [58, 59], while none has also included psychoeducational VR experiences. However, psychoeducation is considered the first step intervention for managing stress and anxiety, with benefits for reducing the intensity of these conditions [66, 67].

Within this context, this randomized controlled trial (RCT) aims to investigate the efficacy and acceptability of a home-based VR training for managing stress and anxiety during the COVID-19 pandemic in a sample of Italian healthcare workers. The intervention will consist of three training sessions performed in a week. In each session, participants will try through an immersive VR standalone system (i.e., Oculus Quest 2), a virtual psychoeducation experience on stress and anxiety (i.e., MIND-VR) [50], followed by a virtual content for relaxation (i.e., The Secret Garden) [64].

### Objectives

The primary objective of this RCT focus on the usefulness of the proposed home-based VR intervention for decreasing stress and anxiety and for enhancing the knowledge about these conditions compared to a control group. The secondary objective is to assess the acceptability of the home-based VR training.

## Methods/design

The study is registered in the ClinicalTrials.gov database (NCT04611399) and has received ethical approval from the Institutional Review Board Committee (IRBC) of the University of Milano-Bicocca, the Foundation IRCCS Carlo Besta Neurological Institute Foundation, and the Istituto Santa Lucia (Roma, Italy). The study will be conducted based on the CONSORT guidelines [68]. If there are any amendments during the trial, they will be registered on ClinicalTrials.gov.

### Design and setting

The study will follow a 2-arm, parallel-group, RCT model. A total of 60 consecutively enrolled individuals (see the “Sample size” section for the power calculation) will be recruited from healthcare workers of three Medical Sites (MS) in Italy: the Foundation IRCCS Carlo Besta Neurological Institute Foundation (Milan, Italy), the Fondazione Europea Ricerca Biomedica (FERB) (Gazzaniga, Italy), and the Istituto Santa Lucia (Roma, Italy). In each MS, 20 participants will be recruited among hospital units that treat or have treated COVID-19 patients (i.e., the emergency department, surgical units, and critical care units).

